| 
Intervention:
 | 
In spite of the difficulty to purchase antigen RDT, we were able to receive tests from three different brands that are all CE approved. In order to test the three different brands, and therefore have stronger generalization ability, we will rotate RDT brand use after 33 patients recruited. We started with the RDT from Roche (Standard Q COVID-19) (https://www.roche.com/media/releases/med-cor-2020-09-01b.htm), and then switch to RDTs from Abbott (Panbio COVID-19 Ag) (https://www.globalpointofcare.abbott/en/product-details/panbio-covid-19-ag-antigen-test.html) and then to those from AAZ-LMB (COVID-VIRO) (http://www.covid19aaz.com/). After 99 patients, we will start the cycle again and so on.
 
Saliva sample collections will be performed following the guidance published in Ott et al (2020) and Kojima et al (2020). Instead of collecting only saliva in a tube, the patient will perform him/herself a swab of the gingiva-buccal fold, under the supervision of a healthcare worker. A pilot test is ongoing at Unisanté to ensure appropriateness of swab type and procedure. The results of the first 10 positive patients done as a pilot show perfect concordance between PCR results on saliva and nasopharyngeal samples, with 1-3 log viral load less in saliva. Now that we got the RDT, we will follow the pilot on a few samples for RDT analysis on saliva.
 
No coughing or sniffing prior to sample collection is required. Ideally, water should be avoided 10 minutes prior to collection. Other drinks, food, and nasal sprays should be avoided 20 minutes before sample collection.
 
The health care worker must wear a personal protection equipment (at minimum, mask and gloves) prior to contact with the patient. The patient must clean his/her hands using alcohol-based sanitizer or soap and water (no fragrances).
 
The health care worker should verify all collection material labelling (at minimum, patient name/identifier and date and time of collection) with the patient. While preparing collection materials, he/she directs the patient to begin pooling saliva in his/her mouth.
 
If the RDT are available and Swissmedic granted, the following sampling procedure will be performed:
 
 
1) A first swab will be done on saliva by the patient using the 4 zones (gingiva-buccal fold left and right, tongue and palate) for 30 seconds to perform PCR (see video from 1:14 https://coronavirus.delaware.gov/drive-thru-testing-instructions-for-curative-test-english/).
 
2) The second swab will be on saliva collection. The health care worker will open the RDT kit, give the swab to the patient that will pass it for 30 seconds in the 4 zones of the gingiva-buccal fold. The health care worker will perform immediately the RDTs according to the manufacturer instruction as above, e.g (Standard Q COVID-19) (Roche/SD Biosensor : https://www.youtube.com/watch?v=mBdaOHJWxI4).
 
3) The third swab will be done on nasopharyngeal fluid by the health worker to perform PCR (reference test).
 
4) The fourth swab will be done on nasopharyngeal fluid by the health worker to perform the RDT. He will perform immediately the RDTs according to the manufacturer instruction.
 
 |

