
|                                               |                                                                                                                                                                                                                                                                                                                                                                                                                                                                                                                                                                                                                                                                                                   |
|-----------------------------------------------|---------------------------------------------------------------------------------------------------------------------------------------------------------------------------------------------------------------------------------------------------------------------------------------------------------------------------------------------------------------------------------------------------------------------------------------------------------------------------------------------------------------------------------------------------------------------------------------------------------------------------------------------------------------------------------------------------|
| Number of Participants with Rationale: | 
250 SARS-CoV-2 positive patients by any method (RDT on saliva, PCR on saliva, PCR on nasopharynx), which corresponds to ~1250 patients enrolled with
 
 
- 1250 saliva samples for RDT
 
- 1250 saliva samples for PCR
 
- 1250 nasopharyngeal samples for RDT
 
- 1250 nasopharyngeal samples for PCR
 
 
The expected prevalence will be 20% SARS-CoV-2 positive patients by any means (RDT on saliva or nasopharynx, PCR on saliva or nasopharynx)
 
It should be possible to recruit the study subjects relatively easily considering the number of patients who come for testing at Unisanté sites.
 |

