### 2.3 Competent Ethics Committee (CEC) and Competent Authorities (CA)

**Protocol approval.** The principal investigator ensures that approval from an appropriately constituted Competent Ethics Committee (CEC), and Swissmedic is sought for the clinical study OclinC.

**Protocol changes.** No changes are made to the protocol without prior approval from the Sponsor and CEC, except where necessary to eliminate apparent immediate hazards to study participants. Such urgent changes to the protocol due to immediate hazards must be reported to the Sponsor within 48h. According to Oclin art. 37 safety and protection measures which must be taken immediately will be notified to CER-VD.

**Unanticipated risks/benefits.** This is an observational prospective trial that features very little additional risk to the patient. The collection of saliva swabs is innocuous. The standard procedure for nasopharyngeal swab can be accompanied (very rarely) by lesion of the nasal mucosa. It definitely leads to some discomfort, or even pain, for the patient.

Should this study show a case detection rate for SARS-CoV-2 using RDT on saliva of at least 70% of that using the standard method (nasopharyngeal PCR), this new method could be proposed as standard diagnostic testing procedure for testing of ambulatory COVID-19 suspected cases to the cantonal and national health authorities, as well as to the national COVID-19 task force. It should ease the work of the testing teams and lead to less

discomfort for patients, and hence probably higher rate of testing readiness from symptomatic patients. The overall testing expenses per person will also be considerably reduced.

The threshold of 70% has been chosen to take into account that RDT on saliva or PCR on saliva are expected to have an overall detection rate lower than that of naso-pharyngeal PCR, but possibly much higher if patients with very low viral loads (e.g. 1000 copies/ml) are excluded from the analysis (Jacot et al, in press). The detection of the virus in the latter patients is indeed fluctuating strongly from one sample or one moment to another. Moreover, they probably contribute much less to transmission than patients with higher viral loads.

A particular effort will be made to expedite reporting and wide communication, given the global urgency of the COVID-19 testing situation.

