### 3.2 Determination of Sample Size

|                              |                                                                                                                                                                                                                                                                                                                                                             |
|------------------------------|-------------------------------------------------------------------------------------------------------------------------------------------------------------------------------------------------------------------------------------------------------------------------------------------------------------------------------------------------------------|
| Sample size predicted | 
250 SARS-CoV-2 positive patients (from either RDT or PCR on saliva and nasopharynx) corresponding to ~1250 patients enrolled
 
 
- 1250 RDT on saliva samples
 
- 1250 PCR on saliva samples
 
- 1250 RDT on nasopharyngeal samples
 
- 1250 PCR on nasopharyngeal samples
 
 |
|------------------------------|-------------------------------------------------------------------------------------------------------------------------------------------------------------------------------------------------------------------------------------------------------------------------------------------------------------------------------------------------------------|

Currently the number of tests performed daily in the canton de Vaud are >1000 at the different triage sites.

At Unisanté, in week 35, we had 398 tests performed at Bugnon 44 with 55 positive (14%), and 749 performed at the Flon with 80 positives (11%), irrespective of symptoms. At Centre Médical de la Source and Vidy-Med, at least 100 patients are tested every day.

The proposed sample size of 250 positive among 1250 cases tested will allow to have a precision of  $\pm 2\%$  on the detection rate if the latter is 20%, based on a confidence interval of 95%.

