##### Secondary outcome:

- Viral loads (number of copies/ml) of SARS-CoV-2 by sample type, namely PCR saliva and PCR nasopharyngeal swabs

Viral loads will be compared between the two sample collection methods using the Kruskal-Wallis rank test. Pearson correlation coefficient will also be used to compare viral load values using the two methods.

Stratified analysis of detection rates will be performed. Detection rates of the two RDT methods will be calculated according to two virus load categories ( $<36$  Ct value,  $\geq 36$  Ct value)

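### Pearson's r is assigned to compare saliva and nasopharyngeal viral loads, but it cannot register a constant 10- to 1000-fold deficit, and neither planned statistic estimates how much virus saliva sampling loses

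*Protocol*

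**What the plan says.** Section 3.3.1 of the protocol, under Secondary outcome, defines the endpoint as "Viral loads (number of copies/ml) of SARS-CoV-2 by sample type, namely PCR saliva and PCR nasopharyngeal swabs". Two analyses follow. The first is a test: "Viral loads will be compared between the two sample collection methods using the Kruskal-Wallis rank test". The second is the coefficient: "Pearson correlation coefficient will also be used to compare viral load values using the two methods". The section names no log transformation, paired difference, ratio or limits of agreement.

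The Intervention part of the synopsis reports what the pilot found in its first ten positive patients. PCR results were fully concordant, but "with 1-3 log viral load less in saliva".

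Section 2.3 links detection to viral load. It expects saliva methods to detect fewer cases overall and singles out "patients with very low viral loads (e.g. 1000 copies/ml") as a group in which detection fluctuates strongly.

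**The concern.** The coefficient is given a task it cannot perform. To compare viral loads between two sampling routes, one needs to know how far apart they are and how much that gap varies between patients. Pearson's r answers another question: whether patients who are high on one route are also high on the other. A high r is compatible with saliva carrying a tenth, a hundredth or a thousandth of the virus.

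This matters because the pilot already suggests a deficit of 1 to 3 log10, and because the protocol uses viral load to explain why saliva tests may miss cases. The useful result is the size of the loss. The other planned statistic does not supply it either: a Kruskal-Wallis test gives a p-value for a shift, treats each patient's two samples as independent groups, and estimates nothing.

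A second, conditional concern is scale. The only unit named is copies/ml. Viral loads spread over several orders of magnitude, so a product-moment correlation on that scale is governed by the few largest values.

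**Working it through.** **The plan's own figures.** The protocol gives no sample size, target or threshold for the viral load correlation. Its enrolment figure reproduces: 250 / 0.20 = 1250. The stated precision of ±2% is 1.96 × √(0.2 × 0.8 / 1250) = 2.2 points, which agrees after rounding. Nothing below depends on these figures.

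**Step 1: r is blind to a constant deficit (exact, no assumptions).** For any factor c > 0,

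corr(X, cY) = c·cov(X, Y) / (s_X · c·s_Y) = corr(X, Y).

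On the log scale the deficit is a shift d, and cov(x, y − d) = cov(x, y) with both SDs unchanged. A check on one simulated set of 250 pairs (nasopharyngeal log10 mean 6, SD 2; residual SD 1):

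| Saliva lowered by | r, log10 | r, copies/ml | Mean paired log10 difference |
|---|---|---|---|
| 0 log | 0.904 | 0.869 | +0.03 |
| 1 log | 0.904 | 0.869 | −0.97 |
| 2 log | 0.904 | 0.869 | −1.97 |
| 3 log | 0.904 | 0.869 | −2.97 |

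The paired difference follows the deficit and r does not move.

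**Step 2: what happens on the copies/ml scale (conditional).** The documents give no spread for viral load, so these inputs are assumptions, shown over a range: 200 pairs quantified in both samples; nasopharyngeal log10 load normal with mean 6 and SD 1, 1.5 or 2; saliva lower by a uniform 1 to 3 log10 (the pilot's range), with residual SD 0.5 or 1; 3000 data sets per row. The share is of the nasopharyngeal sum of squares, Σ(X − X̄)². Concordance is Lin's coefficient on log10, which penalises a systematic gap.

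| SD | Residual SD | Median r, log10 | Raw r: 5th / 50th / 95th percentile | Median share, top 1 / top 3 | Median change in raw r without top 3 | Raw r > 0.9 | Concordance, log10 |
|---|---|---|---|---|---|---|---|
| 1 | 0.5 | 0.79 | 0.19 / 0.53 / 0.95 | 55% / 85% | 0.18 | 8% | 0.30 |
| 1 | 1 | 0.66 | 0.03 / 0.25 / 0.87 | 57% / 86% | 0.14 | 4% | 0.27 |
| 1.5 | 0.5 | 0.89 | 0.21 / 0.68 / 0.99 | 74% / 96% | 0.24 | 23% | 0.50 |
| 1.5 | 1 | 0.79 | 0.05 / 0.38 / 0.99 | 74% / 96% | 0.23 | 13% | 0.46 |
| 2 | 0.5 | 0.93 | 0.23 / 0.78 / 1.00 | 85% / 98% | 0.26 | 36% | 0.64 |
| 2 | 1 | 0.87 | 0.06 / 0.51 / 1.00 | 85% / 98% | 0.30 | 23% | 0.60 |

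With 250 pairs the results are almost the same. Raw r varies widely between repetitions of the same truth. Even r on log10, which is stable, stands well above the concordance coefficient in every row, because it omits the gap.

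**Step 3: would the companion test see the shift?** With 200 pairs, SD 1.5 or 2, residual SD 1 and a constant shift of 1, 2 or 3 log10, the Kruskal-Wallis test rejected at 5% in all 500 simulated data sets of each setting.

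**Step 4: pairs with one negative PCR.** With a mean saliva load of 6 − 2 = 4 log10 and variance SD² + residual SD² + 1/3 (the last term from the uniform deficit), the share of saliva values below 1000 copies/ml (3 log10) is about Φ((3 − 4)/1.26) = 21% at SD 1 and residual 0.5, and Φ((3 − 4)/2.31) = 33% at SD 2 and residual 1. The protocol does not call 1000 copies/ml a detection limit, only a level at which detection fluctuates. Under these assumptions discordant pairs would not be rare.

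**The case against.** The strongest reply is that r is not the only comparison, nor the first. The preceding sentence gives the location question to Kruskal-Wallis, and Pearson is an addition. Step 3 indicates that a shift of the pilot's size would be flagged, and the protocol already discloses the deficit. This stands. A reader might infer that the plan would hide the deficit, or would lead to a finding of close agreement between the two routes. The documents do not support that, because r would have to be read without the test result beside it.

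Second, the raw scale is an inference. Copies/ml is the unit of the outcome; nothing says the values stay untransformed, and the pilot result is itself expressed in logs. A transformation may properly be left to an SAP. This also stands, so Step 2 is conditional. A log scale would remove the dependence on extreme values, but it would not touch Step 1.

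Third, raw r is not systematically inflated. It exceeded r on log10 in only 13% to 31% of data sets, so it understates the association more often than it overstates it. A reader should not infer a bias towards apparent agreement; the fault is instability.

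Fourth, no decision rests on r. The 70% criterion in section 2.3, the primary hypothesis in section 3.1 and the interim rules in section 3.3.2 all use detection rates. That limits the weight of the point.

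What none of this answers is that Kruskal-Wallis discards the pairing and yields no estimate, so the size of the loss goes unreported.

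**Conclusion.** The point holds as a minor one on a secondary outcome. Pearson's r is stated as a means of comparing viral loads, and it cannot measure the difference at issue. That is a mathematical property, needs no assumption, and applies on either scale. The companion test would probably detect a shift but neither uses the pairing nor sizes the difference. As written, section 3.3.1 would not say how many logs of virus are lost by sampling saliva, or how much that loss varies between patients.

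The dependence on a few samples is conditional on r being computed in copies/ml and on the assumed spread. Over log10 SD 1 to 2, the top three of 200 pairs hold about 85% to 98% of the nasopharyngeal sum of squares. The 5th to 95th percentile range of raw r is 0.19 to 0.95 at SD 1 with residual 0.5, and 0.06 to 1.00 at SD 2 with residual 1. The primary detection-rate analysis is unaffected.

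**What to change.** In section 3.3.1, under Secondary outcome:

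- Analyse viral load as log10 copies/ml.
- Report the mean within-patient difference (saliva minus nasopharynx) with its 95% CI and Bland-Altman limits of agreement among pairs positive in both samples, with differences plotted against means. Back-transformed, the mean difference is the fold loss.
- State what happens to pairs with one negative PCR: report them separately by direction, or treat the negative value as censored at the detection limit. Without such a rule, the pairs with the largest saliva deficit tend to drop out and the mean loss is understated.
- Keep any correlation on log10 values, or use Spearman's, and label it as association only.

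The cost is a sentence or two in the protocol and slightly more analysis work. No further patients, samples or measurements are needed. The price is one of scope: the limits of agreement describe only pairs quantified in both samples unless the censoring is modelled.

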### 3.3.3 Deviation(s) from the original statistical plan

In this urgent situation we must be flexible and to respond to important emerging questions on new potential interventions.

Modifications may have to be made to ensure the robustness of the findings, seek confounding factors and respond to emerging trends in the data.

## 4. ADVERSE EVENTS

### 4.1 Definition and assessment of adverse and other safety related events

#### 4.1.1 Definition and severity of Adverse events (AEs)

An AE in this case is any untoward medical occurrence in a volunteer, which may occur during or after medical procedure performed with an investigational medical device and does not necessarily have a causal relationship with the intervention. An AE can therefore be any unfavourable and unintended sign (including an abnormal laboratory finding), symptom or disease temporally associated with the study intervention, whether or not considered causally related to the study intervention.

The severity of the adverse events will be recorded according to standard definitions.

#### 4.1.2 Adverse event causality

All AE will be evaluated for causality by the investigational team. In addition, Sponsor (through delegated PV CRO) may make a causality assessment of all SAE. Causality will be assessed according to standard criteria (No relation, possible, probable, and definitely related).

### 4.2 Actions taken in case of adverse events

All clinically relevant AEs will be monitored and handled according to the medical judgement of the clinical investigator.

The volunteer may be followed up more intensively for the purposes of monitoring the evolution of the AE. For example, a telephonic contact may be transformed into a physical visit so that a clinical exam or further blood samples and investigations relevant for the resolution of the AE may be undertaken. Additionally, the volunteer may be referred for specialist assessment.

All actions will be logged and incorporated into the assessment of AE severity

### 4.3 Recording and reporting of adverse events

#### 4.3.1 Recording

All AEs (occurring at any point in the trial) that are observed by the Investigator or reported by the volunteer, whether or not attributed to study procedure, will be documented in the eCRF (REDCap) on specific templates developed for this purpose at Unisanté.

#### 4.3.2 Reporting

AEs will be transmitted to the Sponsor. The Principal investigator (or any delegated site staff) will report immediately and within 24 hours all SAE to the sponsor. SAEs will be reported by email via the RedCap survey tool). All elements captured within the SAE form featured in the eCRF will be transmitted. This includes free text and auxiliary information required for

appropriate assessment of the severity and causality of the SAE. A separate email containing relevant coded source documents (laboratory or radiological exams) will be sent simultaneously. SAEs will be reported to the Ethics Committee via BASEC within 7 days by the principal investigator. Swissmedic will also be informed via the sponsor in this time frame.

## **5. QUALITY ASSURANCE AND CONTROL**

### **5.1 Data handling and record keeping / archiving**

#### **5.1.1 Case Report Forms**

All protocol-required information will be collected directly from a tablet and entered in REDCAP. Other source documents if necessary will be stored securely. Few variables will be collected, namely ID number, phone number, date of birth, date, sex, duration of symptoms, fever (Y/N), cough (Y/N), anosmia a Y/N), ageusia (Y/N), anticoagulation (Y/N), PCR saliva test result (positive/negative and Viral loads), PCR nasopharyngeal test result (positive/negative and viral loads), RDT nasopharyngeal test result, RDT saliva test result,

Only the Sponsor, PIs, investigators, site coordinators and medical professionals will be allowed to access the source documents and database.

Once identifying information is no longer required for the basic functioning of the trial (i.e. the requirement to identify patient, and telephone for result return), all eCRFs will be strictly anonymised and only the participant number in combination with year of birth will remain.

This identifying information that is removed from eCRFs at the end of participant follow-up will be transferred to a separate secured file which is independent from the eCRFs. And this will be made available only under request to the PI (if the request pertains to pharmacovigilance monitoring, quality assurance reviews, audits or a medical concern of the patient, with the patients consent).

This procedure will be identical for the two new sites, namely the Centre Médical de la Source and Vidy-Med. Indeed, the procedures for result transmission to the patients are handled by the same laboratory for Unisanté and Vidy-Med (Laboratoire de microbiologie). The anonymization and coding can thus be performed in the same manner in all sites.

Only the Sponsor, Investigators, the CER-VD and regulatory authorities will have access to the records.

